## 1 Introduction

The planned analyses and corresponding statistical methods for Study are provided in this Statistical Analysis Plan (SAP).

## 2 Study Introduction

### 2.1 Study objectives

To evaluate the efficacy and safety of Y-2 sublingual tablet in patients with acute ischemic stroke.

### 2.2 Study Design

This study is a multicenter, randomized, double-blind, parallel, placebo-controlled trial.

The study is divided into three periods: Screening/Baseline Period, Treatment Period, and Follow-up Period.

**Screening/Baseline Period:** Subjects enter the Screening/Baseline Period after signing the informed consent form.

**Treatment period:** Screened eligible subjects are randomized to receive Y-2 sublingual tablets (investigational group) or Y-2 placebo (control group) for 14 consecutive days. Performing protocol-required tests and assessing safety during treatment.

**Follow-up Period:** Subjects who finish treatment enter the follow-up period and are followed up until Day 90 from treatment. Stroke related scale scores are performed at 14, 30, and 90 days from the start of the first study drug use, and adverse events are recorded during follow-up to further assess safety.

### 2.3 Study Endpoints

- **Primary Efficacy Endpoint**
  - The proportion of patients with mRS score  $\leq 1$  on Day 90 after randomization.
- **Secondary Efficacy Endpoints**

- mRS score on Day 90 of treatment;
  - the proportion of patients achieving a good functional outcome (mRS  $\leq 2$ ) on day 90;
  - the change in NIHSS score from baseline to 14 days.
  - the proportion of patients achieving an NIHSS score  $\leq 1$  on day 14, 30 and 90 days after randomization.
- **Safety Endpoints**

Safety evaluation include:

- adverse events within day 90.
- treatment related adverse events within day 90.
- changes in vital signs and laboratory data before and after treatment.

According to the protocol, exploratory biomarker studies will also be conducted in parallel in this study, and data collection and analysis will be handled separately and not included in this statistical analysis plan.

## 2.4 Primary Estimated Target

The primary clinical concern of this study is to assess the efficacy of Y-2 sublingual tablet versus placebo in patients with acute ischemic stroke based on the treatment strategy, whether or not the subject experienced a dose delay, interruption, or use of a protocol-allowed concomitant medication (as defined in Protocol Section 5.8.1) due to an adverse event, in terms of the proportion of subjects with mRS score  $\leq 1$  at Day 90 after start of treatment.

The primary estimated target attributes are shown in Table 2- 1.

**Table 2- 1: Primary Estimated Target Attributes**

| Attributes                | Descriptions                                                                                                                                                                                                                   |
|---------------------------|--------------------------------------------------------------------------------------------------------------------------------------------------------------------------------------------------------------------------------|
| Target population  | Adult patients with acute ischemic stroke, the study is limited to all subjects who meet the inclusion and exclusion criteria for the trial and are successfully randomized.                                                   |
| Treatment measures | Y-2 sublingual tablets 36 mg (containing edaravone 30 mg and dexborneol 6 mg) or Y-2 placebo (containing 60 micrograms dexborneol to mimic the cool taste when administered like the investigated drug) BID for 14 consecutive |

|                                            |                                                                                                                                                                                                                                                                                                                                                                                                                                                                                                                                                                                                                                                                                                                                                                                                                                                                                                                                                                                                                                                                                                                                                                                                                                                                                                                                                                                                                |
|--------------------------------------------|----------------------------------------------------------------------------------------------------------------------------------------------------------------------------------------------------------------------------------------------------------------------------------------------------------------------------------------------------------------------------------------------------------------------------------------------------------------------------------------------------------------------------------------------------------------------------------------------------------------------------------------------------------------------------------------------------------------------------------------------------------------------------------------------------------------------------------------------------------------------------------------------------------------------------------------------------------------------------------------------------------------------------------------------------------------------------------------------------------------------------------------------------------------------------------------------------------------------------------------------------------------------------------------------------------------------------------------------------------------------------------------------------------------|
|                                            | 
days for a total of 28 times.
 
Concomitant medications/therapies may be administered during the study (from signing of informed consent through last follow-up) as specified in Section 5.8 of the protocol.
                                                                                                                                                                                                                                                                                                                                                                                                                                                                                                                                                                                                                                                                                                                                                                                                                                                                                                                                                                                                                                                                                                                                                                                      |
| Study Endpoints                     | 
Treat-to-target status was derived based on the mRS score at day 90 after the start of treatment, i.e., a mRS score <math>\leq 1</math> was considered to be treat-to-target.
                                                                                                                                                                                                                                                                                                                                                                                                                                                                                                                                                                                                                                                                                                                                                                                                                                                                                                                                                                                                                                                                                                                                                                                                                           |
| Intercurrent Events and Addressing  | 
 
• The following intercurrent events were managed using a treatment policy strategy, i.e., regardless of whether they occurred or not: 
 
○ Use of concomitant medication/therapy during the treatment period (regardless of whether concomitant medication/therapy is permitted or prohibited), but continue trial drug treatment and follow-up after investigator 's assessment;
 
○ Delayed, interrupted, or discontinued treatment due to an AE, but did not prematurely withdraw from the study;
 
○ Because of the impact of the new coronavirus epidemic, the required time point mRS score could only be obtained by remote visits.
 
 
 
• A composite variable strategy was used to address the following intercurrent events, i.e., the occurrence of such events would be considered as suboptimal mRS scores: 
 
○ No mRS score after start of treatment regardless of cause;
 
○ Premature withdrawal from protocol-specified follow-up due to AEs.
 
 
 
• While-on-treatment strategy, defined as mRS compliance status based on the mRS score closest to the event, was used to handle premature treatment discontinuation or study withdrawal for reasons other than those mentioned above.
 
 |
| Population Level Summary Indicators | 
The proportion of patients achieving a mRS score of <math>\leq 1</math> was summarized for the Y-2 sublingual tablet group and the placebo group based on the mRS score at day 90 after the start of treatment according to the established treatment regimen for 14 days, and the rate difference between the two groups was calculated.
                                                                                                                                                                                                                                                                                                                                                                                                                                                                                                                                                                                                                                                                                                                                                                                                                                                                                                                                                                                                                                                               |

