**2.3. Main estimated target**

The main clinical concerns of this study: Based on treatment policy strategy, the efficacy of Y-2 Sublingual Tablets versus placebo in patients with acute ischemic stroke was assessed by the proportion of participants with an mRS score  $\leq 1$  at Day 90 after treatment, regardless of whether the participants had delayed or discontinued the administration, or used protocol-allowed concomitant medications (as specified in Section 5.8.1) due to adverse events.

The main estimated target consists of the following attributes:

- Population: adult patients with acute ischemic stroke. The study population in this trial is determined by the inclusion and exclusion criteria defined in Section 4;
- Treatment: Y-2 Sublingual Tablets 36 mg (containing 30 mg of edaravone and 6 mg of dexborneol) or Y-2 placebo control (containing 60  $\mu$ g of dexborneol to simulate the cool taste of sublingual administration of the investigational product) BID for 14 consecutive days, 28 times in total;
- Endpoint: treatment compliance status derived from the mRS score at Day 90 after treatment (compliance: mRS score  $\leq 1$ );
- Handling of other concomitant events:
  - Use of concomitant medications/therapies during the treatment period but continued with investigational product treatment and follow-up after

investigator assessment; or delay, interruption of administration, or discontinuation of the treatment due to AEs, but no early withdrawal from the study; or mRS scores at required time points could only be obtained through remote visit due to the impact of COVID-19: Use of treatment policy strategy (regardless of the occurrence of such events);

- No mRS score after initiation of the treatment for any reason; or early discontinuation of treatment or withdrawal from the study due to death; or early withdrawal from protocol-specified follow-up due to AEs: use of a composite strategy (occurrence of such events was counted as a substandard mRS score);
- Early discontinuation of the treatment or withdrawal from the study for reasons other than those mentioned above: use of the while-on-treatment strategy (i.e., mRS compliance status was evaluated based on the mRS score closest to the withdrawal from the study).

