#### **4. Population**

##### **4.1. Inclusion criteria**

Those who meet all the following requirements:

- Age  $\geq 18$  years old and  $\leq 80$  years old, regardless of gender;
- After the onset of the disease, the National Institutes of Stroke Scale score:  $6 \leq \text{NIHSS} \leq 20$ , and the sum of the fifth upper limb score and the sixth lower limb score was  $\geq 2$ ;
- The onset time is within 48 hours (including 48 hours);
- Patients diagnosed as ischemic stroke according to "key points for diagnosis of all kinds of major cerebrovascular diseases in China 2019", with good prognosis after the first attack or the last attack (MRS score  $\leq 1$  before this attack);
- The informed consent approved by the ethics committee was voluntarily signed by the patient or his legal representative.

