**5.7.1. Criteria for discontinuation of or withdrawal from the treatment**

Treatment should be discontinued in the following cases:

1. Intolerable adverse reactions occur during treatment that the investigator concludes that further treatment is not appropriate;
2. Serious violation of the inclusion and exclusion criteria is found after enrollment, and both the investigator and the Sponsor think the treatment needs to be discontinued;
3. New disease changes unrelated to the investigational product occur during treatment that the investigator concludes that further treatment is not appropriate;
4. Interventional therapy (including cerebrovascular stenting) is considered necessary by the investigator during treatment;
5. The subject is unwilling to continue the treatment.

All subjects who have completed the informed consent form and are eligible for enrollment in the trial have the right to withdraw from the clinical trial at any time. The subjects can withdraw from the study if the following conditions are met during the study:

- 1) The subject experiences intolerable adverse reactions;
- 2) The subject asks to withdraw and is unwilling to continue to participate in the study;
- 3) The investigator thinks that the subject cannot complete this study due to poor compliance;
- 4) The subject is lost to follow-up;
- 5) The subject is pregnant;

- 6) The subject participates in other clinical trials;
- 7) The investigator considers that the subject is not appropriate to continue to participate in the study for other reasons.

For withdrawn subjects, the original adverse events will still be followed up, but no other information will be collected, including new adverse events, unless the investigator thinks such events are related to the drug.

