[5] mRS score before this onset.

[6] Completion after SSS TOAST classification and enrolling is acceptable.

[7] Use as soon as possible after randomization.

[8] Concomitant medications and adverse events should be recorded from the time of signing the informed consent form to Day 90 of medication or the last follow-up.

If adverse event occurs, the subject will be followed up until the adverse event disappears or is restored to baseline levels or is not clinically significant.

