### **8.4. Efficacy analysis**

All the analyses were performed in the intention-to-treat population. Missing data on the primary outcome was imputed with treatment policy strategy, composite variable strategies, and while on treatment strategies accounting for intercurrent events, as follows:

- Treatment policy strategy

For the following concomitant events: After the subject is successfully randomized and starts to receive the treatment, concomitant medication/treatment is used during treatment (see Section 5.8) and the investigator does not discontinue the treatment or let the subject withdraw from the study early based on the actual situation; or the subject does not withdraw from the study early despite treatment delay, interruption or discontinuation due to AEs; the subject's mRS score can only be obtained remotely due to the pandemic, The primary efficacy outcomes will be treated by the treatment policy strategy, that is, regardless of whether the concomitant events occur. Whether the mRS reaches the standard will be assessed according to the measured mRS score collected (the mRS score of remote visit is considered valid).

- Composite strategy

For the following concomitant events: Randomized subjects, for whatever reason, do not have an mRS score after the start of the treatment;; or the main reason for the subject's early withdrawal from follow-up prescribed by the protocol is AE, the primary efficacy indexes will be treated by the composite strategy, i.e., the occurrence of such events is considered as

having a mRS score of 6 at the end of follow-up (Day 90 after treatment).

- While on treatment strategy

When a subject discontinues the treatment or withdraws from the study early for reasons other than those mentioned in the composite index strategy, the primary efficacy indexes will be treated by the while on treatment strategy, that is, using the most recent mRS score before the withdrawal from the study as the basis for determining whether the mRS meets the target.

Group difference in the primary efficacy outcome was examined using chi-square test or Fisher exact test, and the corresponding 95% confidence intervals (CIs) of the difference between proportions were estimated based on the normal-approximation. Odds ratios (ORs) with 95% CIs were calculated using logistic regression.

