## 2.5 Sample Size Determination

The sample size for this study was based on the primary efficacy measure, the proportion of subjects with mRS score  $\leq 1$  at Day 90 of treatment. According to previous clinical studies (see Protocol Reference 7-12), it is estimated that the proportion of subjects with mRS score  $\leq 1$  on Day 90 of treatment will be 50% in the investigational group and 40% in the control group, taking a two-sided  $\alpha$  of 0.05, a power of 80%, and a randomization ratio of 1:1. After calculation, 388 subjects are required in each group. Considering a 15% dropout rate, 457 subjects are planned to be randomized in each group, with a total sample size of 914.

An interim analysis is scheduled to be performed after approximately 50% of patients complete the visit on Day 90. The purpose of interim analysis is to re-estimate the sample size based on primary efficacy indexes. It is conducted by the Independent Data Monitoring Committee (IDMC) and whether the sample size should be increased or remain unchanged is recommended according to the regulations of the IDMC. The sample size may be increased to 1.5 times the scheduled sample size at most, and won't be reduced. If the sample size is adjusted, the method proposed by Cui et al. 1999 (hereinafter referred to as the CHW method) will be used to control type I errors in the final analysis.

Interim analyses and sample size re-estimation were performed by an Independent Data Monitoring Committee (IDMC) as detailed in Section 4.5 of this plan and in the IDMC charter.

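### Read literally, the SAP's while-on-treatment rule replaces an observed Day-90 mRS with an earlier score, possibly the pre-stroke one, when a patient stops tablets for a non-AE reason

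*Combined protocol and SAP*

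**What the plan says.** SAP Table 2-1 sorts intercurrent events into three strategies:

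- **Treatment policy** covers delay, interruption or stopping of treatment because of an AE, provided the patient stays in the study. It also covers concomitant therapy while trial drug continues, and remote visits.
- **Composite** counts as not meeting the target any patient with no mRS after the start of treatment, and any patient who leaves follow-up because of an AE.
- **While-on-treatment** takes the remaining cases: it is "defined as mRS compliance status based on the mRS score closest to the event, was used to handle premature treatment discontinuation or study withdrawal".

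SAP 4.3.1, protocol 2.3 and protocol 8.4 use the same double trigger. Protocol 8.4 words it as "When a subject discontinues the treatment or withdraws from the study early for reasons other than those mentioned in the composite index strategy". They differ on which score to use (see the working).

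Protocol 6 schedules the mRS at Visit 1, Day 14 (+3), Day 30 and Day 90, with none at the Day 7 visit. The Visit 1 entry is footnoted "mRS score before this onset". Protocol 4.1 admits patients "with good prognosis after the first attack or the last attack", which it defines as an mRS of at most 1 before this attack. The SAP 4.3.1 subgroup list accordingly has only the premorbid categories 0 and 1.

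Protocol 5.7.1 lists reasons for stopping treatment separately from reasons for leaving the study. The first list includes the patient's unwillingness to continue.

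**The concern.** The endpoint is functional status at Day 90. A patient who stops tablets early by choice and returns at Day 90 has that status measured. A rule that scores the visit nearest the stop sets the measurement aside in favour of an interim one. Two patients with the same follow-up are then handled differently according to whether an AE prompted the stop.

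The pre-stroke score makes this worse. It describes the patient before the event under treatment, and eligibility guarantees that it meets the target. If it may serve as the nearest score, an early non-AE stop becomes an automatic success. Equal stopping in both arms dilutes the treatment difference. Unequal stopping biases the primary comparison and moves the type I error.

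**Working it through.** **1. Plan's own figure.** SAP 2.5 uses a two-sided alpha "of 0.05, a power of 80%, and a randomization ratio of 1:1", and expects that the success proportion "will be 50% in the investigational group and 40% in the control group". With pooled variance and no continuity correction:

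n = [1.960 × √(2 × 0.45 × 0.55) + 0.842 × √(0.50 × 0.50 + 0.40 × 0.60)]² / 0.10² = 387.3, rounded up to 388. Then 388 / 0.85 = 456.5, so 457 per arm and 914 in total. All three figures reproduce. Power is 80.1% at 388 per arm and 86.1% at 457. The sample size does not depend on the point at issue.

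**2. The four wordings side by side.** All are triggered by stopping treatment or leaving the study for other reasons.

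| Section | Score to be used | Source for a patient who stops tablets but never withdraws |
|---|---|---|
| SAP Table 2-1 | closest to the event | score nearest the stop |
| SAP 4.3.1 | closest to the time of withdrawal | undefined |
| Protocol 2.3 | closest to study withdrawal | undefined |
| Protocol 8.4 | latest before study withdrawal | undefined |

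**3. Which score is nearest.** Place Visit 1 between day -1 and day 1 and the next mRS between day 14 and day 17. The midpoint runs from (-1 + 14)/2 = 6.5 to (1 + 17)/2 = 9. Before about the end of week 1 the nearest score by date is the pre-stroke one, if it is allowed. After that it is usually the Day-14 score.

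**4. Who is affected by a week-1 stop.**
- No mRS after the start of treatment: failure under the composite rule.
- Left the study for a non-AE reason with an mRS at the withdrawal visit (protocol 6.3.2 asks dropouts to attempt the Visit 5 items): that score is the closest.
- Stopped tablets for a non-AE reason and still followed: pre-stroke success, but only under the Table 2-1 wording and only if the pre-stroke score is eligible.

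Only the third group is at issue.

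**5. Size.** Let f be the share of an arm in that third group. The documents do not give f, so every value is an assumption. Suppose these patients' true Day-90 success rate equals that of their arm. The analysed rate is then p' = p + f(1 - p).

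*Equal f, true rates 50% and 40%, 457 per arm.* At f = 5%: 0.50 + 0.05 × 0.50 = 0.525 and 0.40 + 0.05 × 0.60 = 0.430, a difference of 0.095.

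| f in each arm | Difference (points) | Power |
|---|---|---|
| 0% | 10.0 | 86.1% |
| 1% | 9.9 | 85.3% |
| 2% | 9.8 | 84.5% |
| 5% | 9.5 | 82.1% |

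*Unequal f, both true rates 40%.* The spurious shift is 0.60 × (f on drug - f on placebo). For 5% v 2% the rates are 0.430 and 0.412, a shift of 0.018. The pooled and unpooled standard errors are both about 0.0327, so the upper-tail error is 1 - Φ[(1.960 × 0.0327 - 0.018)/0.0327] = 1 - Φ(1.41) = 7.9%.

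| f, drug v placebo | Shift (points) | Upper-tail error | Two-sided error |
|---|---|---|---|
| equal | 0 | 2.5% | 5.0% |
| 2% v 1% | +0.6 | 3.8% | 5.4% |
| 4% v 2% | +1.2 | 5.6% | 6.6% |
| 5% v 2% | +1.8 | 7.9% | 8.5% |
| 2% v 5% | -1.8 | 0.6% | 8.5% |

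Substitution by a Day-14 score is not quantified here, because the plan gives no Day-14 success rate.

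**The case against.** The best defence is that overriding Day 90 was never intended. Only Table 2-1 anchors to the event, while the other three sections anchor to withdrawal, which a patient still in follow-up does not have. Protocol 8.4 and SAP 4.3.1 also present the strategies as handling of missing data, and the endpoint throughout is the Day-90 mRS. This stands as evidence of intent. It does not remove the Table 2-1 wording or the double trigger, and nothing confines the rule to missing Day-90 scores.

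Use of the pre-stroke score is also an inference: no section permits it and none forbids it. The name of the strategy, and the composite rule for patients with no mRS after the start of treatment, suggest that it was not meant to count.

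Three stronger readings are tempting but not supported:

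- **That early stoppers in general are scored as successes.** Step 4 of the working shows otherwise.
- **That patients who deteriorate and need a procedure become successes**, because protocol 5.7.1 lists "Interventional therapy (including cerebrovascular stenting) is considered necessary by the investigator during treatment" among its reasons for stopping. Protocol 7.3.1 treats a disease that leads to an operation as an AE, and likewise worsening beyond what was expected. Most such patients who remain in the study would keep their Day-90 score under treatment policy. Expected stroke progression is the possible exception.
- **That the rule flatly contradicts the headline of protocol 2.3**, "regardless of whether the participants had delayed or discontinued the administration". That sentence ends by referring to adverse events, as does its counterpart in SAP 2.4, so non-AE stopping may lie outside it.

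Finally, sensitivity analyses 1 to 4 impute only missing Day-90 outcomes. They appear to keep observed scores and could expose a discrepancy, but they do not correct the primary result. Analyses 3 and 4 carry the last observation forward, again without barring the pre-stroke score.

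**Conclusion.** The concern holds in a limited form. As written, SAP Table 2-1 can override an observed Day-90 mRS for patients who stop tablets for a non-AE reason and stay in follow-up. It does not exclude the pre-stroke score as the replacement, and it conflicts with three other statements of the same rule. Different programmers could follow the text and obtain different primary results.

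Neither the size nor the direction of bias can be fixed from the documents. Rare and balanced stops cost little: 1% to 2% in each arm takes power from 86.1% to between 85.3% and 84.5%. Imbalance matters more, and its sign follows the arm with more such stops. The figures assume that the literal reading is applied, the pre-stroke score is allowed, and stoppers have average outcomes for their arm. The planned 15% dropout is a different quantity and should not be read as an estimate of f.

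**What to change.** Reconcile protocol 2.3, protocol 8.4, SAP Table 2-1 and SAP 4.3.1 so that all four state:

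1. The observed Day-90 mRS is used for every randomised patient who has one, whatever the reason for stopping study drug.
2. A substitute score applies only when the Day-90 mRS is missing.
3. Only an mRS recorded after the first dose may be substituted, never the pre-stroke mRS. Randomised patients with no post-randomisation mRS count as failures.

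The cost is protocol and SAP wording and some programming. It needs no extra patients or visits, and the sample size stays at 388 evaluable and 457 randomised per arm, 914 in total.
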